### Economic impact

In addition to the individual benefits for patients, the AS strategy also generates cost savings, as already demonstrated in economic studies [19, 20].

An assessment of the economic impact of implementing the AS strategy will be carried out by comparing the costs related to this treatment with the costs of immediate treatments, such as radiotherapy and prostatectomy, in patients with low-risk prostate cancer. For this, in addition to mapping the resources allocated to patients in the prospective AS cohort, a retrospective collection of medical records will also be carried out to assess the resources allocated to patients who underwent prostatectomy or radiotherapy from January 2013 to January 2022. Both arms of this substudy will involve considering the costs of medical evaluation, exams, procedures and hospitalizations related to the follow-up of prostate cancer.

### Perceptions of urologists regarding AS

In this study, we will assess the perception of urologists at the participating centres regarding the indications of AS prostate cancer patients in the public health system. For this, each urologist will sign an ICF and answer an online questionnaire at the beginning and end of the study.

### Data analysis and statistics

Descriptive analysis will be used to characterize the study population, with categorical variables presented as absolute (n) and relative (%) frequencies, variables with normal distribution presented as the mean and standard deviation, and variables with asymmetric distribution presented as the median and interquartile range.

We will examine data normality using the Shapiro‒Wilk normality test. The Chi-square test will be applied to detect differences between outcomes and predictor variables with a statistical significance level of 0.05 for all comparisons. Nonparametric tests will be used when appropriate.

Survival analysis will be used to analyse treatment-free survival, overall survival, cause-specific survival and metastasis-free survival. The results will be presented by graphing the estimated survival function and its respective 95% confidence interval (CI).

Budget impact analysis (BIA) will be conducted according to the International Society for Pharmacoeconomics and Outcomes Research (ISPOR) [21] guidelines and Canadian guidelines.

### Sampling and sample size

Considering the rate of pathological reclassification of patients on AS as the main outcome, the estimate for the sample size was 200 patients, using a significance level of 5%, an estimate for the rate of pathological reclassification in 12 months of 24% [18] and an acceptable difference of 10%, to obtain a sample power of more than 80%.

The sample size of 454 medical records for BIA was calculated using the estimate that approximately 30–40% [22] of patients do not need to undergo interventional treatment, with a power of 80%, a significance level of 5% with an acceptable difference of 5% and a design effect of 1.3. Considering that from these records it is possible to have a percentage of missing data, 10% was added, resulting in a final number of 500 reviewed records, approximately.

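### The 454-record economic sample is sized for a ±5-point confidence interval, so its stated 80% power plays no part, and the proportion it is sized on is not what the records supply

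*Protocol article*

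**What the plan says.** The section Sampling and sample size of the protocol article gives two calculations. The second is for the budget impact analysis. It opens "The sample size of 454 medical records for BIA was calculated using the estimate" and takes as its planning value that about 30–40% "of patients do not need to undergo interventional treatment". The remaining inputs are stated as "with a power of 80%, a significance level of 5% with an acceptable difference of 5% and a design effect of 1.3". A further 10% for missing data brings the total to about 500 records.

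The section Economic impact describes the only retrospective record review in the article. Its purpose is to "assess the resources allocated to patients who underwent prostatectomy or radiotherapy from January 2013 to January 2022", so that the costs of immediate treatment can be compared with those of active surveillance (AS). The section Data analysis and statistics adds that the budget impact analysis will follow published guidelines. It names no hypothesis test for this substudy.

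**The concern.** Two things do not fit together.

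- **Power.** The article prints a power, a significance level, a difference and a design effect as if all four produced 454. If the number comes from a confidence-interval width, the power figure is not a property of the sample and should not be printed beside it.
- **Target quantity.** The calculation is built on a proportion of patients who need no intervention, but the records are of men who were operated on or irradiated, and are read for resources used. A precision of 5 percentage points for a proportion says nothing about how precisely a mean cost will be known.

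The Discussion says the economic evaluation can help guide public policy. A reader could therefore credit the cost results with 80% power or 5-point precision when the calculation supports neither for costs.

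**Working it through.** **Inputs** (Sampling and sample size): n = 454; proportion 30–40%; power 80%; significance level 5%, sidedness not stated and taken as two-sided; difference d = 5 percentage points; design effect 1.3; 10% added for missing data. The value p = 0.35 is the midpoint of the range and is inferred.

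**1. Reproducing 454.** The size for a 95% confidence-interval half-width d is n = 1.3 × 1.96² × p(1 − p) / d².

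- p = 0.35: 3.8416 × 0.2275 / 0.0025 = 349.6; × 1.3 = 454.5 (454.4 with the unrounded normal quantile)
- p = 0.30: 322.7 × 1.3 = 419
- p = 0.40: 368.8 × 1.3 = 479

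The midpoint gives the published figure and the ends of the range do not. Power does not enter. The missing-data step also agrees: 454 × 1.10 = 499.4, about 500.

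**2. Power of 454 records for a 5-point difference.** The effective size is 454 / 1.3 = 349.2. For a one-sample test of p0 against p1, power = Φ[(|p1 − p0| − 1.96√(p0(1 − p0)/349.2)) / √(p1(1 − p1)/349.2)].

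- 35% vs 40%: (0.05 − 0.0500) / 0.0262 ≈ 0, power 50.0%
- 35% vs 30%: power 50.0%
- 30% vs 35%: (0.05 − 0.0481) / 0.0255 = 0.08, power 53%
- 40% vs 35%: (0.05 − 0.0514) / 0.0255 = −0.05, power 48%

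Exact binomial power at n = 349 is 46–49% for the two comparisons from 35%.

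**3. What 80% power would correspond to.**

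- Detectable difference at p = 0.35: (1.96 + 0.8416) × √(0.2275/349.2) = 2.8016 × 0.02552 = 0.0715, about 7 points.
- Size for 5 points: n = 1.3 × (1.96√(p0(1 − p0)) + 0.8416√(p1(1 − p1)))² / 0.05². This gives 944 for 35% vs 40% and 907 for 35% vs 30%.

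**4. More favourable readings.**

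- One-sided 5%: power 60–65%.
- Design effect ignored: 58–64% two-sided, at most 74% one-sided.
- Two-sample comparison of 30% with 40% at 80% power and design effect 1.3: 459–463. This is near 454, but it is per group (918–926 in total) and uses a 10-point difference, not the stated 5.

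None of these gives 80% power for 5 points with 454 records.

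**5. What the records can support.** For a mean cost with coefficient of variation CV, the relative 95% half-width is 1.96 × CV × √(1.3/n). The documents give no CV and no split between treatments. The CVs below, an even split, and the use of the 1.3 design effect for costs are assumptions.

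| Assumed CV | All records, n = 454 (0.105 × CV) | One treatment, n = 227 (0.148 × CV) |
|---|---|---|
| 0.5 | ±5.2% | ±7.4% |
| 1.0 | ±10.5% | ±14.8% |
| 1.5 | ±15.7% | ±22.2% |

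**The case against.** The strongest reply is that nobody plans to test this proportion. The substudy is a cost comparison and a budget impact analysis. A sample sized by a 95% half-width d always has about 50% power to detect d, so the 50% exposes no hidden shortfall. **This stands.** A reader might infer that the substudy is underpowered and needs some 907–944 records. The documents do not support that, because those figures answer a test that is not planned. They show only that the printed power cannot be right as stated.

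A second reply concerns the sampled population. A reader might infer that the planning proportion is zero by construction, since every man in the review was treated. That goes too far: not needing treatment is not the same as not receiving it, and the source cited for 30–40% is not available. The article also does not say outright that the 454 are the records described under Economic impact, although it describes no other record collection. What survives is narrower: the sizing proportion is not the resource use and cost for which the records are reviewed.

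Third, one might move the proportion to the 200-man AS cohort and quote ±7.5 points. That borrows a design effect stated only for the records; without it the figure is 1.96 × √(0.2275/200) = ±6.6 points. It also treats as a fixed proportion something the article analyses as treatment-free survival, with follow-up it admits will initially be short. Neither figure should be inserted.

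Lastly, p = 0.35 is inferred, and strict rounding up would give 455. The match is close enough that this changes nothing.

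**Conclusion.** The point holds in a limited form. The 454 is a ±5-point confidence-interval size at 35% with design effect 1.3, and the 80% power played no part in it. Taken literally, the statement overstates power by about 30 percentage points (80% against about 50%). This rests on p = 0.35 and a two-sided test, but no alternative reading tried rescues the figure. The 5-point precision also belongs to a proportion, not to the costs the records are collected to provide; that step relies on the 454 being the records described under Economic impact.

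This should be fixed but is not critical. The abstract lists economic impact as exploratory. The primary outcome, its 200-patient sample and the planned number of records are unaffected.

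**What to change.** In Sampling and sample size:

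1. Keep about 500 records and delete the power clause. Describe 454 as the size at which a 95% confidence interval for a proportion of 35% has a half-width of 5 percentage points, with design effect 1.3.
2. State that this precision does not apply to the cost results.
3. Give the expected precision of mean cost as 1.96 × CV × √(1.3/n), for all records and separately for prostatectomy and radiotherapy. State the CV and the expected split as assumptions.
4. Take the proportion remaining untreated from the AS cohort's treatment-free survival estimate with its own 95% confidence interval, and quote no fixed half-width for it in advance.

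The change is to wording only and adds no records. The authors must supply a CV and an expected split between treatments, and the stated basis will look less favourable than 80% power.

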### Monitoring

Monitoring will be carried out remotely by the coordinating centre. Monitoring is expected to occur on a quarterly basis for each centre participating in the study. In this stage, we will analyse data integrity, verifying whether the data are attributable, readable, contemporary, original and accurate in relation to the source documents. Data reports will be automatically generated using R software, enabling simultaneous monitoring of any missing and inconsistent data.

## Discussion

This is the first Brazilian prospective study of patients with prostate cancer under AS. The study will include centres that are part of the public health system in which many patients are not offered the AS strategy due to insecurity regarding the accuracy of the exams and adherence of patients to monitoring. Data also show that discrepancies in the Gleason score usually occur in approximately 14.7% of biopsy revisions [23]. This study includes a pathological review of all prostate biopsies and a review of mpMRI images. The outcomes of AS will be quantified to assess the applicability of this treatment. The study will also involve evaluating the perception of urologists regarding AS in the public health system and assessing the main problems, which may help health managers plan future improvements.

Brazil is a large country of great diversity and a mixed race population, and this is, to our knowledge, one of the largest AS study cohort with a majority of nonwhite patients. AA men have worse prostate cancer outcomes, which leads to uncertainties in the indication of AS [24]. As large prospective studies have included few AA men, it is generally reported that more prospective observational studies are required before definitive conclusions can be reached [25]. We aim to help understand the clinical outcomes of AS in populations of different races and socioeconomic statuses.

The study has some limitations. Initially, it will have a short follow-up time, but we will seek to extend the duration of the study to obtain long-term outcomes. The Brazilian population is large and involves great diversity between regions, but the study will seek to balance the inclusion of patients. The study will mainly include patients who exclusively use the public health system, but this group represents the majority of the Brazilian population.

A strength of the study is the dissemination of knowledge about AS, a practice considered standard of care in low-risk prostate cancer, which may help to preserve the quality of life of Brazilian men. The data gathered by the study can be used for future investigations in the Brazilian population. Economic impact evaluation can help guide public policies in the country. Important data will be collected on the sociodemographic profile of the population and on the treatment profile currently being applied in the public health system.

## Data Availability

Not applicable.

## Abbreviations

AS: Active surveillance
PSA: Prostate-specific antigen
DRE: Digital rectal examination
mpMRI: Multiparametric MRI
AA: African American
ICF: Informed consent form
CCI: Charlson comorbidity index
PRIAS: Prostate Cancer Research International Active Surveillance
IHC: Immunohistochemistry
PTEN: Tensin homologous phosphatase
CI: Confidence interval
CA: Caucasian American
